### States for the MSMs

States will capture 3 types of events related to SUD care: initial states, transient states, and terminal states. Defining states requires a balance of specificity to produce actionable information, and parsimony to allow for an estimable statistical model with accurate estimates and smaller SEs.

Initial states in the MSMs represent the clinical settings that triggered an incident event at the start of an SUD care episode, corresponding to the 5 subcohorts in Table 1.

There are 3 types of transient states. The first type is care states, which include different types of care provided in the health care system to treat the SUD, defined by combinations of setting and service type (Table 2). We opted to define 15 preliminary SUD care states based on a combination of 3 settings and 5 service types. The second type of transient state is temporary discontinuation of care. Entry into the temporary discontinuation care state is triggered using a clinically meaningful threshold for time elapsed between SUD treatment visits. The last transient state is SUD remission, which represents an improvement in the patients’ disease.

**Table 2. T2:** Transient states and terminal states are represented in the multistate models.

Category	States included	Description
Transient states	A total of 17 transient states include 15 care states derived from crossing 5 service types with 3 care settings; temporary discontinuation of SUD^a^ care; and remission of use disorder.	Care states Service types Evaluation and assessment Behavioral treatment and counseling Prevention, education, and case management Pharmacotherapy Other service Settings Outpatient Intensive outpatient Inpatient or residential Other transient states Discontinuation of SUD care A lack of SUD care over a specified period^b^ Remission of use disorder Low risk score on alcohol and substance use screen; clinically meaningful reduction on screening scores or <2 symptoms on *DSM-5*^c^ checklist; SUD remission diagnosis
Terminal states	4 states representing the end of a care episode	Death, derived from dates in health care enrollment records or Washington State death data Loss to follow-up, defined as at least 31 days without KPWA insurance coverages Ceased SUD care (no medication fills or services with a qualifying SUD diagnosis for more than 194 days Administrative censoring (in the middle of a care episode when data collection ends)

a SUD: substance use disorder.

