### Study Outcomes

This study has 2 types of outcome assessments: outcomes associated with terminal states, such as the percentage of patients or time that it takes to get to a terminal state, and outcomes associated with pathways, such as achievement of guideline-concordant care (Table 2, Multimedia Appendix 1). Terminal states are explicitly modeled as states in MSMs, whereas the probability of receiving guideline-concordant care is derived from estimated transition probabilities (see subsection Aim 2. Generate Data-Driven Insights to Improve Care Delivery Using Estimated MSMs under the Statistical Analysis section).

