### Statistical Analyses

#### Aim 1: Apply MSMs to Comprehensively Characterize SUD Care Transitions

Separate MSMs will be run for each of the 5 subcohorts specified in Table 1. The 5 subcohorts are mutually exclusive. All prespecified states that are anticipated will be considered. States may be collapsed to address states with a small number of events, and new states may emerge if they occur with sufficient frequency (eg, concurrent receipt of pharmacotherapy and behavioral treatment and counseling). When collapsing or expanding states, we will strike a balance between clinical interpretability and reliable parameter estimation. As a general guideline, ≥40‐50 transition events from *S*_*j*_ to *S_j_* per covariate helps ensure stable hazard ratio estimates and corresponding SEs, but if collapsing states compromises the clinical interpretability of the results, we will adopt a more permissive threshold of at least 10 transition events per covariate for modeling [58]. This criterion will first be applied to define states; specifically, a minimum of 40 (or 10 under the more permissive threshold) transition events is required to define a state, allowing inclusion of 1 covariate in the transition model. When transitions are sufficient to include covariates in the model, at least 40 × *m* transition events are required. Covariate selection for each transition model, given the number of transitions, is described below. Follow-up time or care episode duration is defined as the interval from entry into the initial state (time 0) to entry into a terminal state.

Figure 1 provides a graphical representation of a simplified MSM illustrating potential care pathways. In this example, patients who meet the inclusion criteria and are identified as having an incident SUD in primary care enter the initial state *C*_1_. Patients then transit into 1 of 15 care states (*S*_1_, ... ,*S*_15_) defined by a service type and setting. From these states, patients may transition to temporary discontinuation of care, *D*, or an SUD remission state, *R*. Transitions between the transient states (care states, temporary discontinuation, and SUD remission) are bidirectional, whereas any transition to a terminal state (*T*_1_, ..., *T*_4_) is unidirectional, reflecting that patients cannot leave terminal states once they are entered in MSMs. At the end of follow-up, patients occupy 1 of the 4 terminal states.

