**Figure 1. F1:**
[figure not shown]
Graphical representation of the multistate model. Notation: Subcohort: [*C*_*1*_; care states (*S*_*1*_,...,*S*_*15*_); discontinuation of care: *D*; SUD remission state: *R*; terminal states: (*T*_1_,...,*T_4_*); *t*: time, *p*: probability] The 3 dots connecting the states indicate that the depicted relationships are possible for the other states not shown in this figure. p: probability; SUD: substance use disorder; t: time.

We will adopt a semi-Markov assumption [59] under which transition intensities depend on only the duration that patients spend time in the current state before transitioning. This framework allows transition intensities to vary over time rather than assuming constant transition intensities as in the Markov framework. Time is defined as the duration since entry into a state, with the clock reset to 0 upon entry into the cohort and each subsequent state. At any time since entry into the initial state, a patient occupies 1 of the 21 states (17 transient states and 4 terminal states). Movements between states *j* and *k*
$\left(j,k=S_{1},\ldots ,S_{15},D,R,T_{1},\ldots ,T_{4}\right)$, are governed by a 21-by-21 matrix of transition intensities $q_{jk}(t,z(t))$, which is a function of time *t* and covariates z(t). Intensities capture the instantaneous probability of moving from state *j* to *k*.

Under the semi-Markov assumption, we will fit separate flexible parametric survival models [60,61] for each transition:

$\log\{q_{jk}(t,z(t))\}=s(\log(t)|\eta ,k_{0})+\beta^{T}z_{i}(t)$.

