To assess model adequacy, we will compare spline-based estimates of the cumulative baseline hazard with nonparametric estimates derived from the Kaplan-Meier method for visual agreement. To evaluate the proportional hazards (time-independent effects) assumption, we will test for time-dependent effects by including interactions between covariates and spline functions of time. If these interaction terms are not statistically significant at the 5% level, they will be excluded from the final model.

Additionally, we assume that transition times are exactly observed. Lastly, it is assumed that the distribution of health care visit times is independent of transition probabilities for simplicity (noninformative visiting process). We will primarily use the R (R Foundation) package *flexsurv* to implement the MSMs and develop our own modules to transform the fitted results to answer research questions.

We will consider sensitivity analyses if sample size and other feasibility constraints permit. This includes stratified analyses by subgroups defined by the number of outpatient visits (eg, patients with more visits may have poorer health) [65,66] or clinically meaningful periods. For instance, impactful operational changes occurred due to COVID-19 mitigation restrictions (eg, reduced in-person care), so we will consider estimating models before, during, and after these restrictions were in place. Additionally, stratified analyses by SUD type will be considered to acknowledge that each substance may sometimes require unique forms of care, such as pharmacotherapy usage.

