Table 4 summarizes estimates that can be obtained from fitted MSMs to generate our inferences and answer additional research questions. We will calculate point estimates and CIs and further characterize variation in output quantities across states graphically.

**Table 4. T4:** Summary of multistate model output quantities.

Output	Description	Example question answered
Intensity matrix	Instantaneous probability of moving from 1 state to another	How likely is a transition from an initial primary care state to a behavioral treatment and counseling care state over a small incremental unit of time?
Transition probability matrix	Probability of moving from 1 state to another over a specific time duration	What is the probability of moving from an initial primary care state to a behavioral treatment and counseling care state within 14 days of SUD^a^ identification?
Hitting probability	Point estimate of the probability of ever reaching a state	What is the probability of ever reaching pharmacotherapy during a care episode?
Mean sojourn time	Mean length of time a patient stays in a state	On average, how long does a patient stay in the evaluation and assessment care state before transitioning to another state?
Restricted mean transition-free time	Mean length of time a patient spends in transient states before reaching a terminal state	What is the average time before a patient ceases SUD care after receiving pharmacotherapy?
Expected first passage time	Expected days until hitting a specific state of a set of states	How long until a patient receives SUD pharmacotherapy?
Expected number of visits	Expected number of times a state is reached between 2 given times	What is the predicted number of times behavioral treatment and counseling are reached in the first 30 days of a care episode?
Survival plot	Probability of not reaching a state, as a function of time	How is the probability of not ceasing SUD care after their index SUD event?

a SUD: substance use disorder.

How does the accessibility of each state vary? We will use the models to describe how the accessibility of each state varies by estimating the dynamics of transitioning between different types of care for SUD. We will report and characterize variation in (1) transition probabilities, (2) hitting probabilities, (3) mean sojourn time, (4) expected first passage time, and (5) expected number of visits (definitions in Table 4).

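### The data cut-off is modelled as an absorbing terminal state, so long-horizon and pathway probabilities depend on the cut-off and entry dates as well as on care

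*Protocol article*

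**What the plan says.** Table 2 (States for the MSMs) gives four terminal states: death, loss to follow-up, ceased SUD care, and "Administrative censoring (in the middle of a care episode when data collection ends". Four statements elsewhere show that this is more than a label:

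- Study Outcomes: "Terminal states are explicitly modeled as states in MSMs".
- Statistical Analyses, Aim 1: "patients cannot leave terminal states once they are entered in MSMs", and "At the end of follow-up, patients occupy 1 of the 4 terminal states". No separate censored status is left over.
- Same section, after Figure 1: "At any time since entry into the initial state, a patient occupies 1 of the 21 states (17 transient states and 4 terminal states"). The article adds that all moves within this set, terminal states included, "are governed by a 21-by-21 matrix of transition intensities", with a separate flexible parametric survival model fitted for each transition.
- Same section: under the semi-Markov assumption, intensities depend only on time already spent in the current state, with the clock reset at every entry.

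Aim 2 then builds on these states. Its quantities include the hitting probability (Table 4: "Point estimate of the probability of ever reaching a state"), state occupancy over time, restricted mean survival time (RMST) from a care state to each terminal state, and the probability of pathways that finish in a specific terminal state. Study Outcomes adds the percentage of patients who reach a terminal state and the time taken. Nowhere does the article say that the cut-off is right-censored in the likelihood or left out of the derived quantities.

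**The concern.** The end of data collection says nothing about the patient. In a time-to-event likelihood it belongs in the censoring indicator. As an absorbing state it competes with death, ceasing care and loss to follow-up, and permanently takes probability that belongs to them.

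It also conflicts with the plan's own model. Time from state entry to the cut-off is fixed by the calendar date of entry. Two patients with the same time in the same state, one entering in 2018 and one in 2025, face quite different times to the cut-off. An intensity that depends only on time in state cannot describe that transition.

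At stake are the combined quantities of Aim 2, and through them the choice of pathways for Aim 3 sampling, which uses pathway probabilities and the probability of reaching negative terminal states. RMST to the administrative-censoring state would describe only the data extract. Any stratification by entry period would mix differences in follow-up with differences in care.

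**Working it through.** **1. The plan's own count.** Care states: 5 service types × 3 settings = 15. Adding temporary discontinuation and remission gives 17. Adding four terminal states gives 21, as stated. Without administrative censoring the count is 17 + 3 = 20. The stated 21 is therefore reached only if the cut-off is a state.

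**2. What is not affected.** Each transition has its own model. In the model for, say, transition to death, an exit to any other state ends observation as censoring. Calling the cut-off a state or a censoring time leaves that likelihood unchanged, so intensities and hazard ratios for real transitions stand. The difference arises when all intensities out of a state are combined.

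**3. Share of episodes ending in the censoring state, by entry period.**

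From the protocol: entry from 1 January 2017 to 31 May 2025 (Quantitative Study Population); preliminary data collection complete by May 2026 and final by November 2027 (Results). No follow-up end date is fixed, so both are used, taken at mid-month.

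Assumed, not in the protocol: exponential episode length with mean *m*; uniform entry within each period; periods cut at 1 March 2020 and 1 October 2022.

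If potential follow-up in a period runs from *a* to *b* years, the share unfinished at the cut-off is

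*m* × [exp(−*a*/*m*) − exp(−*b*/*m*)] / (*b* − *a*).

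For *m* = 2 and data end May 2026:

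- Latest period, *a* = 0.956, *b* = 3.619: 2 × (0.620 − 0.164)/2.663 = 0.34.
- Earliest period, *a* = 6.204, *b* = 9.366: 2 × (0.0450 − 0.0093)/3.162 = 0.023.
- Apparent fall in real terminal outcomes with no true change: 34.3 − 2.3 = 32 points.

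| Mean episode | Data end May 2026: early / middle / late | Fall (points) | Data end Nov 2027: early / middle / late | Fall (points) |
|---|---|---|---|---|
| 0.5 year | 0% / 0% / 2.8% | 2.8 | 0% / 0% / 0.1% | 0.1 |
| 1 year | 0.1% / 1% / 13% | 13 | 0% / 0.2% / 3% | 3 |
| 2 years | 2% / 9% / 34% | 32 | 1% / 4% / 16% | 15 |
| 3 years | 8% / 20% / 48% | 40 | 5% / 12% / 29% | 24 |

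**4. Effect on the probability of ceasing care, whole cohort.** Assumed constant hazards per year: ceasing care *h* = 1.0, death 0.02, loss to follow-up 0.10, so *H* = 1.12. Entry is uniform over *A* = 8.41 years and data end *L* years after entry closes.

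- Ever ceasing care, cut-off as right censoring: *h*/*H* = 1/1.12 = 0.893.
- Share absorbed by the cut-off: [exp(−*HL*) − exp(−*H*(*L* + *A*))]/(*HA*). For *L* = 0 this is 1/9.42 = 0.106. For *L* = 2.45 (November 2027) it is 0.007.
- Ever ceasing care, cut-off as absorbing state: 0.893 × (1 − 0.106) = 0.798 for *L* = 0, and 0.893 × (1 − 0.007) = 0.887 for *L* = 2.45.
- Ceasing care by 1 year: 0.602 under right censoring. By simulation with the absorbing state, 0.572 if data stopped on 31 May 2025, and no material change if they run to November 2027.

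**The case against.** The strongest reply is that the defect reaches less far than it first appears. Most of that reply stands.

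- A reader might infer that the outcome probabilities reflect the cut-off instead of care, or that all the fitted models are biased. The documents do not support this. Separate models per transition leave the real intensities and hazard ratios intact.
- A reader might infer that the terminal-state comparisons across subgroups are biased downward. The example time point is 1 year after cohort entry. Entry closes on 31 May 2025, so with data to May 2026 or later almost nobody can be administratively censored before 1 year. Outputs at 7, 14, 30, 60 and 90 days are likewise barely touched.
- A reader might take the COVID-19 period analysis as planned and certain to show a spurious change. The text says only "we will consider estimating models before, during, and after these restrictions were in place", subject to feasibility, and does not say whether periods follow index date or calendar time of transition.
- The sizes come from the raw share of unfinished episodes, not from the fitted clock-reset models, and rest on assumed episode lengths. Since an episode closes after more than 194 days without SUD care, short means are plausible, and a 0.5-year mean gives under 3 points.
- The study is exploratory and allows states to be collapsed or added.

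None of this supplies a rule that right-censors the cut-off. The state definition is affirmative and appears consistently in Table 2, the text and the matrix dimension, so it is not a detail left to another document.

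**Conclusion.** The point holds in this limited form. As written, the plan makes the end of data collection an absorbing outcome and gives it an intensity that its own semi-Markov assumption cannot represent. Long-horizon occupancy, ever-reaching probabilities, pathway probabilities ending in a specific terminal state and the percentage reaching a terminal state then depend on cut-off and entry date as well as on care.

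The size cannot be fixed from the protocol, which gives neither a follow-up end date nor an episode length. It is small up to 1 year if data run to May 2026 or later. It grows for long episodes, recent entrants and any stratification by entry period. The illustrative range between earliest and latest entry periods, from under 3 points to 40 points, depends on the assumed exponential mean (0.5 to 3 years), the assumed period cuts and the two possible data ends.

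**What to change.** Remove administrative censoring from the terminal states and state that the data cut-off is right censoring in every transition model. Change Table 2, Figure 1, the statements about four terminal states and the matrix dimension to match: 3 terminal states, 20 states in all, 20-by-20. Replace the sentence that every patient ends in a terminal state with one that allows an episode to be censored in a transient state.

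Where strata with different follow-up are compared, report probabilities at horizons that follow-up supports in each stratum. There is no need to drop every ever-reaching probability: within a care episode, the three remaining terminal states bound that quantity.

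The cost is a wording change and one fewer set of transition models, with no new data. The small downside is that some long-horizon quantities will rely on extrapolation from the fitted intensities or must be restricted to a fixed horizon.

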### Data Used to Construct States

#### Health Care Encounter Data

We will use health care encounter data drawn from KPWA EHR data and health care insurance claims to construct initial states, transient states, and terminal states. Data elements include *ICD-10* (*International Classification of Diseases, Tenth Revision, Clinical Modification*) diagnosis codes, health care service procedure codes, encounter type classifications (eg, inpatient, ambulatory, virtual visit, or ED), encounter subtypes (eg, urgent care), departments (eg, mental health), clinical specialty (eg, mental health, social worker, or psychiatry), revenue codes, and place of service codes. Visit timestamps are used in models to determine follow-up time and transition times.

#### Substance Use Data

Patient self-reported substance use frequency, patient self-reported SUD symptoms, and clinician-documented SUD diagnoses will be used to construct states. In the creation of initial states, diagnosis codes, service procedure codes, and revenue codes help determine whether a given health care visit was related to SUD. For instance, some initial states are defined by a new clinician-documented SUD diagnosis, while others are also defined to capture clinical workflows where patients are first identified as having substance use by the nature of a health screening (eg, substance use screening in primary care). Care states require an accompanying clinician-documented SUD diagnosis, unless the care state involves a procedure or medication that is solely indicated for SUD (eg, outpatient addiction treatment or disulfiram medication). The SUD remission state is captured using self-reported substance use frequency and SUD symptoms, and clinician-reported SUD remission diagnoses.

To obtain patient self-reported substance use frequency data, clinicians are prompted by the EHR to conduct annual screening with patients in primary care. During in-person visits, screenings are administered on paper or tablet by medical assistants, then entered into the EHR. In telephone or video visits, patients complete a questionnaire via an online patient portal. Validated substance use screening measures assess past-year alcohol, cannabis, and other drug use [32,39,40]. Patients with screening scores that are deemed to be at high risk for SUD are asked to complete a follow-up assessment for symptoms of SUD using the Alcohol Symptom Checklist and the Substance Use Symptom Checklist, respectively. These 11-item checklists capture symptoms of SUD that align with the 11 *DSM-5* diagnostic criteria [41]; the cutpoint of 2 or more symptoms is consistent with SUD. The checklists have demonstrated strong psychometric properties [42-44].

#### Clinician-Documented SUD Diagnoses

SUD diagnoses include clinically documented *ICD-10* diagnoses for alcohol, cannabis, opioid, stimulant, sedative, and other drug use disorder (eg, inhalants or hallucinogens), which are recorded in the EHR and claims data when clinicians conduct visits. SUD diagnoses will include those identified in the alcohol, opioid, and other drug “abuse and dependence” value sets from the HEDIS (Healthcare Effectiveness Data and Information Set) developed by the National Committee for Quality Assurance [45,46].

#### Death Data

Death, classified as a terminal state in the MSM, will be ascertained from the Washington State Department of Health death data. These data are available for all patients, regardless of whether they remain enrolled in the health system. Following standard practice [47], death data are triangulated from several data sources. Reliability of death date (excellent, fair, or poor) is determined based on the source, the number of reporting sources, and the strength of the match in the matching process (eg, no discrepancies in identifiers).

